### Recruitment {15}

All eligible youth will be informed about the JoyPop app and the study by waitlist case managers through various modalities including mailed and e-mailed letters/flyers and phone calls. Youth will be informed about the study once they are added to the waitlist for mental health service at Dilico and periodically while they wait for services (i.e., when waitlist case managers contact clients to check in).

## Assignment of interventions: allocation

### Sequence generation {16a}

Participants will be randomly allocated in a 1:1 ratio to the control (UP) or intervention (UP + JoyPop) condition. Stratified block randomization will be used to randomly assign participants to each condition. Randomization will be conducted by a researcher not affiliated with the trial using a computer-generated sequencing tool [45].

### Concealment mechanism {16b}

Implementation of the allocation sequence will be managed by a researcher not affiliated with the trial. Once the sequence is generated by the sequencing tool, the researcher will place individual allocations into numbered, opaque, sealed envelopes. Envelopes will be stored in a lock box that only the research assistant determining allocation will have access to.

### Implementation {16c}

After participants complete the measures at pre (baseline), the research assistant will obtain and open the next sequenced envelope to determine the allocation and inform the participant.

## Assignment of interventions: blinding

### Who will be blinded {17a}

Given the nature of this trial, it is not possible to blind participants to their allocation. As measures are self-report, blinding of outcome measures is also not possible. Protection against bias will occur by blinding investigators to condition (i.e., only research assistants directly managing participants will be unblinded). The statistician conducting the analyses will be blinded to conditions.

### Procedure for unblinding if needed {17b}

Not applicable as participants and research assistants will not be blinded to condition.

## Data collection and management

### Plans for assessment and collection of outcomes {18a}

Data will be collected via hard-copy, self-report measures for participants in both conditions. For those in the intervention condition, app usage data will also be obtained through the back-end app database. The research assistant that meets with participants at Dilico will explain how to complete the measures and will be available to answer any questions. Measures are described above in the “Outcomes {12}” section. Measures can be found within the sources cited above.

### Plans to promote participant retention and complete follow-up {18b}

To support retention, participants receive reminders via text/email to return to Dilico and complete measures at each timepoint. In addition, participants will receive cash compensation at each timepoint ($20 baseline; $25 mid; $30 post), as cash incentives enhance the completion of outcome measures in randomized trials [46, 47]. While we had some success with this approach in our pilot studies [44], we will provide a bonus $25 if all timepoints are completed as a further incentive [48]. The principal investigator and research assistants will also have weekly meetings to discuss the trial and monitor retention to determine if additional strategies to promote retention are required. If transportation is a barrier for participants, a taxi will be booked and paid for (through in-kind contribution from our partner organization).

### Data management {19}

A research assistant will transfer participant responses from the hard-copy measures into an online questionnaire hosted via Survey Monkey. The information systems and technical infrastructure for Survey Monkey are hosted within SOC 2 accredited data centers [49]. Physical security controls at the data centers include 24 × 7 monitoring, cameras, visitor logs, entry requirements, and dedicated cages for Survey Monkey hardware. Survey Monkey encrypts data in transit using secure TLS cryptographic protocols. App data will be stored on a password-protected server within Canada. App data is encrypted during transmission. Upon receipt, app data will be saved and stored on a password protected computer. In accordance with the Ownership, Control, Access, and Possession (OCAP™) [50] standards set by the First Nations Information Governance Centre, all electronic data obtained from Indigenous youth will be stored on a password protected computer at Dilico. All hard-copy data will be stored in a locked filing cabinet at Dilico. In accordance with Lakehead University’s policy, data will be retained for at least 5 years following the completion of the research.

### Confidentiality {27}

Confidentiality will be maintained throughout the study in accordance with the Canadian Tri-Council Policy Statement: Ethical Conduct for Research Involving Humans [32] and Thunder Bay Regional Health Sciences Centre and Lakehead University ethical guidelines. All participants will be provided an ID number at the beginning of their participation. All data (surveys and app data) will contain only this ID number. The log linking participant IDs to identifiers will be stored separately from study data and destroyed following data collection. One limitation to confidentiality is if participants endorse recent suicidal thoughts on the symptoms screening measure. If this occurs, the research assistant will notify the clinical services case manager from Dilico. Participants will be informed about confidentiality, the limits to confidentiality, and measures taken to protect their confidentiality, during the informed consent procedure.

### Plans for collection, laboratory evaluation, and storage of biological specimens for genetic or molecular analysis in this trial/future use {33}

Not applicable. Biological specimens will not be collected.

## Statistical methods

### Statistical methods for primary and secondary outcomes {20a}

An independent, contracted, statistician will lead the analyses. Linear mixed modeling will be used to test hypotheses related to emotion regulation, mental health symptoms, and treatment motivation. Polynomial contrasts will be used to test for linear and quadratic changes over time. Effect sizes will be calculated using the Cohen’s *d* formula adapted by Feingold [51]. In the economic analysis, mental health services utilization and their costs during the 4-week period among participants in each condition will be estimated. Then, the incremental costs/savings associated with receiving the app using a cost-consequence analysis will be estimated [52].

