### Objectives {7}

The primary objective of this study is to determine the effectiveness of the JoyPop app compared to usual practice (UP; monitoring) in improving emotion regulation among Indigenous youth (12–17 years) awaiting mental health services. Based on our past research [25, 28], we hypothesize that youth receiving the app will show significantly greater improvement in emotion regulation compared to youth receiving only UP.

The secondary objectives are to (1) compare change in mental health difficulties and treatment readiness between youth in each condition to better understand the app’s broader impact as a waitlist tool and (2) conduct an economic analysis to determine whether receiving the app while waiting for mental health services reduces other health service use and associated costs.

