### Intervention description {11a}

The control condition (UP) involves participants being monitored through existing waitlist management practices in place at Dilico (i.e., regular phone calls to check in and assess functioning). The intervention condition (UP + JoyPop) involves participants being monitored through existing waitlist management practices in place at Dilico plus receiving access to the JoyPop app. The app is currently only available for iOS devices (iPad, iPhone, iPod). If participants do not have access to their own iOS device, they will be provided with a refurbished iPhone for the duration of the study. The refurbished iPhones contain only the JoyPop app (no other features available/enabled). Participants in the intervention condition will be asked to use the app at least twice daily for 4 weeks but will otherwise not be provided with requirements related to app usage. The app incorporates evidence-based features that support improved emotion regulation [25] including Rate My Mood, Journaling, Breathing Exercises, Art, SquareMoves, SleepEase Circle of Trust, and Call for Help (see Fig. 1 for description of features).

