The treatment readiness subscale of MYTS is 4 items (e.g., “I want help finding solutions for my current problems”) and asks respondents how strongly they agree or disagree with each statement on a 5-point scale ranging from 1 (*strongly disagree*) to 5 (*strongly agree*). The subscale score ranges from 4 to 20 with higher scores indicating greater readiness.

The service utilization scale is 5 items and asks respondents about the frequency of healthcare services utilization (i.e., number of visits for/with: walk in clinic, family doctor or nurse practitioner, emergency department, mental health counselor, mental health hotline/phone support) over the prior 2 weeks. Items will be analyzed individually and as a total score across service types.

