## Discussion

In Northwestern Ontario, Indigenous youth access mental health services less often and have longer waits than youth in other areas of the province. Limited access and extended waits can lead to negative outcomes and impact engagement. There is recognition that innovative approaches are needed to help address mental health needs for Indigenous youth. In partnership with Dilico Anishinabek Family Care, we are evaluating the impact of a mobile mental health app (JoyPop) as a tool for youth who are waiting for mental health services. Should findings show that using the JoyPop app benefits Indigenous youth who are waiting for services, and is cost-effective, there may be support to continue offering it more broadly.

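### The economic analysis is worded to cost mental health services only, while its objective and its measure cover health service use more broadly

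*Protocol article*

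**What the plan says.** Objectives {7}, and the Abstract in similar terms, set the economic question: "whether receiving the app while waiting for mental health services reduces other health service use and associated costs".

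The Secondary outcomes part of section {12} describes the measure: "The service utilization scale is 5 items and asks respondents about the frequency of healthcare services utilization". The five types are "walk in clinic, family doctor or nurse practitioner, emergency department, mental health counselor, mental health hotline/phone support", each counted over the preceding 2 weeks. On their use it adds: "Items will be analyzed individually and as a total score across service types".

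The statistical methods section {20a} gives the economic analysis in two sentences. The first says that "mental health services utilization and their costs during the 4-week period among participants in each condition will be estimated". The second goes on to estimate the incremental costs or savings of receiving the app, by a cost-consequence analysis. The article does not list cost components.

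**The concern.** The objective, the measure and the analysis should cover the same services, and here they do not. The objective concerns services other than those the youth are waiting for, and the scale was built to count a broad set of contacts. The costing sentence then narrows to mental health services.

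If {20a} is followed to the letter, a change in emergency or primary care visits would not enter the cost comparison, although these are the plainest examples of other health service use. If it is not followed, the choice of services to cost is made after the data are in, and the published text could be cited for either choice. The Discussion makes support for offering the app more widely depend partly on the economic result, so the set of costed services should be settled beforehand.

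**Working it through.** No figure in the protocol bears on this point, so the check is a comparison of the texts and a count.

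**Inputs**
- Scope of the question (Objectives {7}): other health service use and associated costs.
- Scope of the measure (Secondary outcomes): five service types.
- Scope of the costing ({20a}): mental health services and their costs, over 4 weeks.

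**Step 1. Match each measured type to the wording of {20a}.**

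| Service type on the scale | A mental health service by name? | Costed if {20a} is read literally? |
|---|---|---|
| Walk-in clinic | No | No |
| Family doctor or nurse practitioner | No | No |
| Emergency department | No | No |
| Mental health counselor | Yes | Yes |
| Mental health hotline or phone support | Yes | Yes |

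Costed: 2 of 5. Not costed: 5 − 2 = 3 of 5.

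**Step 2. Could the phrase be shorthand for any visit made for mental health reasons?** As described, the scale counts visits by type of service and does not ask the reason. A general visit therefore could not be sorted into or out of that category from these data.

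**Step 3. Does another section supply the missing costing?** The mixed models in {20a} are for emotion regulation, mental health symptoms and treatment motivation. The Secondary outcomes text promises analysis of the service items but no costs. Section {20b} plans no additional analyses and leaves only subgroup analyses open. The two economic sentences in {20a} are the only costing described.

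**Step 4. Do the collected data allow the wider costing?** Yes. Each form looks back 2 weeks, and forms are completed after 2 and after 4 weeks, so the mid and post forms together cover 2 + 2 = 4 weeks, the period named in {20a}. All five types are on every form.

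**Step 5. Direction of the error.** If the app reduces the three uncosted visit types, leaving them out hides savings. If it increases them, leaving them out hides added cost. The protocol gives no basis for choosing between the two.

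**The case against.** The strongest reply is that this is loose wording in a condensed article. The five-item scale is the only utilization measure described, so the authors may well mean to cost everything on it. All five items are collected from every participant at each timepoint and are to be analyzed singly and in total, so a shift in emergency or primary care use would be seen. This stands as far as use is concerned. It does not settle costs, because {20a} names a narrower set and nothing else in the article widens it.

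A reader might infer three stronger points, which the document does not support.

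- **The cost of delivering the app is left out, so the analysis leans toward savings.** Loaned devices ({11a}: "they will be provided with a refurbished iPhone for the duration of the study") and daily reminders to use the app ({11c}) do go to the intervention arm only. But the incremental costs or savings of receiving the app can include them. The article neither includes nor excludes them, and an itemized cost list is commonly left to a fuller document. Silence is not exclusion, and the lean toward savings would follow only from exclusion.
- **The objective cannot be answered, or use is only described arm by arm.** The use data are collected and analyzed item by item, and the incremental step is itself a comparison between conditions. The choice of count model or interval method belongs to the analysis plan.
- **The Discussion promises a verdict that the method cannot give.** The text reads "Should findings show that using the JoyPop app benefits Indigenous youth who are waiting for services, and is cost-effective". A cost-consequence analysis sets costs and outcomes side by side and does not by itself yield such a verdict. The sentence is conditional discussion wording, however, not a planned analysis or decision rule.

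**Conclusion.** The conflict in scope is real. As worded, the economic analysis costs 2 of the 5 measured service types and leaves 3 out of the cost comparison, so the cost part of secondary objective 2 is only partly answered. This rests on reading mental health services in {20a} literally, as the counselor and hotline items. The article does not confirm a wider reading, and the scale as described would not support one based on the reason for the visit.

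The direction of any error is undetermined, and its monetary size cannot be computed without unit costs. The primary outcome, the randomization and the data collection are unaffected.

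**What to change.** In {20a}, replace the reference to mental health services and their costs with the use and costs of all five service types on the utilization scale over the 4 weeks, compared between conditions. In the same place, state that the incremental cost includes the cost of delivering the app (loaned devices and reminders). This second clause is a clarification, not the correction of a shown omission.

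The cost is a change of wording and a small extra exercise to find unit costs for the three added service types and for delivery. The utilization data are already collected. The downside is that estimated savings may look smaller once delivery cost is explicitly counted.

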### Interim analyses {21b}

Not applicable. No interim analyses are planned.

### Methods for additional analyses (e.g., subgroup analyses) {20b}

No additional analyses are planned. Subgroup analyses may be explored based on the composition of the final sample and the direction of our community partners.

### Methods in analysis to handle protocol non-adherence and any statistical methods to handle missing data {20c}

All randomized participants will be included in analyses (i.e., intent-to-treat). Missing data will be handled with full information maximum likelihood estimation—a preferred method that results in relatively unbiased parameters and valid model fit [53, 54].

### Plans to give access to the full protocol, participant-level data, and statistical code {31c}

The full trial protocol will be available publicly (e.g., through clinicaltrial.gov and BMC Trials). In accordance with OCAP™ [50], data will be retained by Dilico Anishinabek Family Care. Data will not be shared with any third parties.

## Oversight and monitoring

### Composition of the coordinating center and trial steering committee {5d}

[name], as the principal investigator, will be responsible for oversight and management of all research activities. [name] will supervise and meet with the research assistants weekly. Research assistants include undergraduate and graduate students. [name] will consult with co-investigators quarterly to plan for and discuss ongoing trial management. Co-investigators include [name], [name], [name], [name], [name], and [name]. [name] will also consult with the local community partner collaborators quarterly regarding implementation. The trial steering committee includes collaborators [name], [name], and [name], along with the principal investigator and co-investigators.

### Composition of the data monitoring committee, its role and reporting structure {21a}

Investigators will monitor the trial. [name] will meet with the research assistants weekly to discuss recruitment, retention, and data collection. Given minimal risks associated with the intervention, a formal data monitoring committee was not developed.

### Adverse event reporting and harms {22}

No anticipated harms are associated with participating in the trial. If a participant feels upset during or after the study, they will be encouraged to contact relevant support services. [name] will inquire about adverse events during weekly meetings with research assistants. Research assistants are also directed to inform [name] of any concerns or adverse events as soon as they occur. If an adverse event were to occur, [name] would submit the Research Ethics Local Serious Adverse Event Reporting Form to the Thunder Bay Regional Health Sciences Centre Research Ethics Board.

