### Provisions for post-trial care {30}

All participants remain on the waitlist for services with Dilico; thus, most will likely receive care post-intervention (unless they choose not to once services are offered). There are no expected trial-related harms.

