#### Descriptive measures

Descriptive information will be obtained through a demographic questionnaire at pre (baseline). Items will assess age, ethnicity, family composition, highest level of education, gender, sex at birth, sexual orientation, and living situation. Symptom presentation will be assessed with the DSM-5 Self-Rated Level 1 Cross-Cutting Symptoms Measures [42] at pre (baseline). The original measure is 25 items; however, we removed one item related to previous suicide attempts as per our community partner’s request. Respondents are asked to rate how much (or how often) they have been bothered by the specific symptoms during the past 2 weeks. Nineteen of the items are rated on a 5-point scale (*0* = *none or not at all; 1* = *slight or rare, less than a day or two; 2* = *mild or several days; 3* = *moderate or more than half the days; and 4* = *severe or nearly every day*). The suicidal ideation and substance abuse items are rated using a “Yes or No” scale. Scores will be summarized across the 12 psychiatric domains (i.e., depression, anger, irritability, mania, anxiety, somatic symptoms, inattention, suicidal ideation, psychosis, sleep disturbance, repetitive thoughts and behaviors, and substance use) and used to characterize the sample.

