### Participant timeline {13}

### Sample size {14}

Our past research suggests a medium effect for the primary outcome [43]. We estimated conservatively in calculating sample size, using *f* = 0.2 (small to medium effect), alpha = 0.05, and power = 0.95 for a 2 (between subjects; treatment condition) by 3 (within subjects; time) mixed design, which approximates the statistical power needed for the planned linear mixed model under the assumption of compound symmetry (i.e., homogeneity of variance and covariance) [44]. Results suggested a sample size of 66 would achieve necessary power. Given our pilot data [34], we estimate 60% retention throughout the study (40% attrition), meaning we will need an initial sample size of 110.

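### Adverse events are described as ascertained only through unblinded staff report, so the recorded counts are likely incomplete and a weak basis for comparing arms

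*Protocol article*

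**What the plan says.** Section {22} of the protocol article gives the adverse-event process. It starts from the position that "No anticipated harms are associated with participating in the trial", and Provisions for post-trial care {30} likewise says "There are no expected trial-related harms". Two routes follow, both through staff. The principal investigator "will inquire about adverse events during weekly meetings with research assistants", and the assistants must tell the principal investigator "of any concerns or adverse events as soon as they occur". For a distressed youth the section says "If a participant feels upset during or after the study, they will be encouraged to contact relevant support services", with no recording step stated. Any adverse event is then submitted to the ethics board on a form whose title refers to serious events.

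Section {17a} says that the research assistants who manage participants are not blinded. Sample size {14} plans on substantial loss: "we estimate 60% retention throughout the study (40% attrition".

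**The concern.** The question described in {22} is put to staff. An event reaches the trial record if an assistant sees it, is told of it or otherwise learns of it. This raises three difficulties.

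- **Completeness.** Minor but relevant events, such as distress set off by an app feature or a reminder, may never be mentioned if nobody asks.
- **Comparability.** Assistants and youth both know the allocation. The app arm receives reminders at 8 am and 8 pm every day, and some of its members hold a study phone. Controls receive only session reminders. Unprompted reports would therefore arise under unequal conditions, and the direction of any resulting difference cannot be predicted.
- **Reach.** Assistants meet youth at sessions, and those who stop attending have no further sessions. The reminders in {11c} and {18b} ask youth to attend; none is described as asking why a youth stopped.

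What is at stake is the meaning of a low or zero adverse-event count. The Discussion looks ahead to wider offering of the app to minors on a waitlist. There is no data monitoring committee {21a} and no independent audit {23} to supply the information another way.

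**Working it through.** **Step 1: the plan's own numbers.** No figure is stated for adverse events. The only figures involved are those in {14}.

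- Inputs: f = 0.2, alpha = 0.05, power = 0.95, a 2 by 3 mixed design, 60% retention.
- For the condition-by-time interaction, lambda = f² × N × m / (1 − rho), with m = 3, df1 = 2 and df2 = 2(N − 2). The article gives no correlation. With an assumed rho = 0.5, N = 66 gives power 0.9504 and N = 64 gives 0.9439, so 66 reproduces. Other assumed values give N = 132 (rho 0), 92 (rho 0.3) and 42 (rho 0.7).
- 66 / (1 − 0.40) = 110, which reproduces exactly.
- Expected leavers: 110 − 66 = 44. With 1:1 allocation and equal attrition, each arm has 55 youth, of whom 22 leave and 33 stay.

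**Step 2: what each described contact could pick up.**

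| Contact | Both arms? | After randomization? | Described as feeding the adverse-event record? |
|---|---|---|---|
| Principal investigator's weekly inquiry {22} | Put to staff | Yes | Yes |
| Assistants' own reports {22} | Depends on what staff learn | Yes | Yes |
| DERS-SF, DASS-21, SDQ, MYTS, service use {12} | Yes | At 2 and 4 weeks | No |
| DSM-5 Level 1 symptom measure {12} | Yes | No | No |
| Partner's routine waitlist calls {11a} | Yes | Yes | No |
| App usage data {18a} | App arm only | Yes | No |

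On the DSM-5 measure the article says "Symptom presentation will be assessed with the DSM-5 Self-Rated Level 1 Cross-Cutting Symptoms Measures [42] at pre (baseline"). Under {16c} the allocation envelope is opened only after the baseline measures are done, so this screen cannot detect anything that follows randomization.

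**Step 3: how much could be lost among leavers (illustration only).** The event rates here are assumptions. The worst case is that every event in a stayer is captured and none in a leaver is. Share missed per arm = 22 × pL / (33 × pS + 22 × pL), where pS and pL are the rates in stayers and leavers.

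| pS | pL | Events per arm | Seen | Share missed |
|---|---|---|---|---|
| 5% | 5% | 2.75 | 1.65 | 40% |
| 5% | 10% | 3.85 | 1.65 | 57% |
| 5% | 20% | 6.05 | 1.65 | 73% |

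**Step 4: what asking would gain.** If n youth are asked and none reports an event, the exact one-sided 95% upper limit for the rate is 1 − 0.05^(1/n). For n = 55 this is 5.3%; for n = 33 it is 8.7%. These limits show the value of a direct question and of reaching leavers. They correct nothing in the article.

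**The case against.** The strongest reply is that this is a condensed article. It refers to a full protocol (version 4) that is not shown, and adverse-event forms, visit scripts and tables by arm commonly belong there or in the analysis plan. That reply stands in part: the lack of a table by arm is not an error in the article. But {22} does state how events are ascertained, and that stated method can be judged.

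A reader might also draw four stronger conclusions, which the text does not support.

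- *Events count only if a youth volunteers them.* Assistants must report "of any concerns or adverse events as soon as they occur", which covers anything they observe or learn. Under {11c} all youth are encouraged to bring concerns to the team.
- *No participant is asked.* The article describes no such question, but nowhere says that none is asked.
- *Harms cannot be compared between arms.* DASS-21, SDQ and counts of emergency department, counselor and hotline use are collected identically in both arms at 2 and 4 weeks. Distress and crisis-service use can therefore be compared among attenders. These measures are only a partial substitute: they are missing for non-attenders, they do not identify a feature or reminder as the source of distress, and the SDQ looks back 6 months in a 4-week trial.
- *Youth who leave are missed.* Leavers stay on the waitlist {30} and may still receive the partner's calls. No link from those calls to the trial record is stated, but none is ruled out. The 44 is a planning assumption across both arms, and with equal attrition half of them would be controls.

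It is also fair to say that the objectives are effectiveness, symptoms, readiness and cost, and that no section promises to establish safety. Sending every adverse event on a serious-event form over-reports to the ethics board and does not lose data. It does leave unstated how non-serious events are recorded.

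**Conclusion.** The point holds as a weakness in the described method. Adverse events are ascertained through unblinded staff report. No systematic question to participants is described, and no adverse-event route is stated for the roughly 40% (44 of 110) expected to leave. Recorded counts are likely incomplete and a weak basis for comparing arms. How incomplete cannot be read from the article; under the assumed rates and the worst case above, 40% to 73% of events per arm would go unseen.

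This rests on the article being a fair account of the process, on attrition near the planned level, and on there being no unstated link from the waitlist calls. It does not affect the sample size, the primary analysis or any stated figure. It should be addressed before any statement about the frequency of harms is drawn from the trial.

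**What to change.** - Add one short open question, identical in both arms, to the mid and post forms, covering unwanted or upsetting events since the last visit.
- Put the same question, with the reason for leaving, to youth who withdraw or miss a session, using the existing text, email or phone contact.
- Tabulate all recorded events by arm.
- State in {22} how non-serious events are recorded, as distinct from those sent on the serious-event form.
- If the full protocol already contains such a question, say so in {22}.

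The cost is one extra item on existing paper forms, a message to non-attenders, one table, and a minor amendment through the ethics board and the partner organization.
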